# Partial wrist denervation versus patient education and self-managed exercise therapy in patients with wrist osteoarthritis: study protocol for a randomized controlled trial

**DOI:** 10.1186/s13063-025-09241-7

**Published:** 2025-10-30

**Keywords:** Osteoarthritis, Wrist, Wrist denervation, Scapho-lunate advanced collapse, SLAC, Scaphoid non-union advanced collapse, SNAC, Exercise therapy, Patient education

## Abstract

**Background:**

Wrist osteoarthritis (OA) is mainly posttraumatic, affects younger individuals than other types of OA, and can lead to significant disability. The first-line treatment is patient education and exercise, but surgery may be considered if symptoms persist. A mini-invasive surgical approach for wrist OA is partial wrist denervation, which, in theory, alleviates pain by resecting sensory nerve branches while preserving movement. Although denervation has shown mixed results, studies suggest improvements in pain and function. However, the long-term efficacy remains uncertain, with a notable percentage of patients requiring further surgical interventions. This randomized controlled trial (RCT) aims to compare the effectiveness of partial wrist denervation to nonsurgical treatment, consisting of patient education and a self-managed exercise therapy program.

**Methods:**

In this multicenter, two-armed, assessor-blinded, superiority RCT, 140 adult patients with symptomatic scapholunate advanced collapse (SLAC) or scaphoid non-union advanced collapse (SNAC) OA are randomly assigned (1:1) to receive either partial denervation through neurectomy of the anterior (AIN) or posterior (PIN) interosseous nerves or patient education combined with a self-managed exercise therapy program focused on wrist stability and muscle strength. The primary outcome is the change in the Patient-Rated Wrist Evaluation (PRWE) score at 6 months. Secondary outcomes include wrist range of motion, grip strength, pain levels, survival of the interventions, and quality of life over 12 months.

**Discussion:**

High-quality evidence regarding the effectiveness of different treatment options in wrist OA is lacking. To our knowledge, this is the first RCT comparing surgical and nonsurgical treatments in wrist OA. Using patient education and exercise therapy as a comparator to partial wrist denervation ensures ethical, clinically relevant care aligning with current OA treatment standards. Ultimately, the findings of this trial will guide and optimize treatment recommendations for wrist OA.

**Trial registration:**

ClinicalTrials.gov ID NCT06098586. Registered on 23 Oct 24.

**Supplementary Information:**

The online version contains supplementary material available at 10.1186/s13063-025-09241-7.

## Introduction

### Background and rationale {6a}

Osteoarthritis (OA) is a chronic, degenerative joint disease and a leading cause of physical disability among adults [1]. There are no treatment options available that can restore a joint damaged by OA. Instead, treatments focus on alleviating pain and enabling a return to a desired lifestyle [2]. OA in the wrist commonly affects the joints surrounding the scaphoid bone and is often caused by a degenerative or posttraumatic injury to the scapholunate ligament or an unhealed fracture of the scaphoid: scapho-lunate advanced collapse (SLAC) and scaphoid non-union advanced collapse (SNAC) [3, 4].

The least invasive surgical option in wrist OA is partial wrist denervation, which aims to reduce articular pain by resection of sensory nerve branches that innervate the wrist joint [5]. It is used either as a primary method for analgesia or combined with proximal row carpectomy (PRC), wrist fusion, or arthroplasty. In contrast to these more extensive procedures, denervation is a minimally invasive surgical technique that preserves joint motion and does not require postoperative immobilization. Studies have shown varied results following partial wrist denervation. Case series and a non-randomized trial including 12–89 participants have reported considerable improvements in patient-reported outcomes (PROMs), pain, grip strength, or motion after resection of the anterior (AIN) or posterior (PIN) interosseous nerves [6–9] or a combined AIN and PIN denervation [5, 10–12]. Conversely, a recent study investigating AIN and PIN denervation found only modest improvements in pain and patient-reported function, with uncertain clinical significance [13]. Further, a systematic review of denervation in posttraumatic wrist OA reported no significant change in pain scores and a decreased range of motion (ROM) after surgery [14]. The long-term effects of partial wrist denervation remain uncertain, as 24–28% of patients require additional surgery within 12–18 months after treatment due to persistence or recurrence of symptoms [13, 15]. Patient education and exercise therapy are recommended as core treatments for all individuals with OA, irrespective of age or symptom severity [2, 16–18]. These treatments have primarily been assessed on individuals with knee and/or hip OA with positive effects such as reduced pain and improved function [19, 20]. For hand OA in general, there is low to moderate evidence that exercise-based rehabilitation is effective for improving pain, stiffness, hand function, and grip strength in the short term [21, 22]. For wrist OA, only 1 RCT comprising 48 participants has evaluated a neuromuscular exercise therapy program as a core treatment [23]. This study found that a neuromuscular exercise program was not superior in reducing pain or improving function compared to a range of motion training program. To our knowledge, no RCTs have compared a surgical intervention to a nonsurgical control in wrist OA, and there is no high-quality evidence supporting the effectiveness of partial wrist denervation or exercise therapy for managing wrist OA.

### Objectives {7}

The aim of this study is to compare partial wrist denervation of the AIN and PIN with a nonsurgical treatment that includes patient education and a self-managed exercise therapy program. The primary objective is to investigate whether partial wrist denervation is superior to patient education and self-managed exercise therapy in improving the Patient-Rated Wrist Evaluation (PRWE) score at 6 months following the start of the intervention. Secondary objectives are to evaluate the superiority of partial wrist denervation over patient education and exercise therapy in terms of pain reduction, quality of life, objective functional outcomes, and treatment survival at the 3- and 12-month assessments.

### Trial design {8}

This is a multicentre, assessor-blinded superiority parallel-group RCT with two treatment arms, adhering to the Standard Protocol Items: Recommendations for Interventional Trials (SPIRIT) [24] and Consolidated Standards of Reporting Trials (CONSORT) guidelines [25]. The overall trial design can be found in the flowchart (Fig. 1) and the SPIRIT diagram (Fig. 2).

**Fig. 1 Fig1:**
[figure not shown]
Flowchart of the trial design

**Fig. 2 Fig2:**
[figure not shown]
SPIRIT diagram of enrolment, interventions, and outcome measures

## Methods: participants, interventions, and outcomes

### Study settings {9}

The study will be conducted at the Department of Hand Surgery, South General Hospital, Stockholm, and the Department of Hand Surgery, Skåne University Hospital, Malmö.

### Eligibility criteria {10}

#### Inclusion criteria

Age ≥ 18 yearsSymptomatic wrist OA (≥ 6 months), due to SLAC or SNAC, grades 1–3Radiological signs of osteoarthritis on posteroanterior and lateral radiographs assessed by the classification of SLAC by Watson et al. [3] and of SNAC by Vender et al. [4]. Radiographs taken 12 months prior to enrolment are eligible. If more than 12 months have passed, new radiographs will be obtained before enrolment.

#### Exclusion criteria

Previous PIN or AIN neurectomyRheumatoid arthritis (RA) or other chronic inflammatory arthritis. History of psoriasis affecting joints, gout, or pseudogoutSymptomatic osteoarthritis in the distal radio-ulnar (DRU), scapho-trapezio-trapezoid (STT), or thumb carpometacarpal (CMCI) jointsOngoing infection in the hand or wristInability to co-operate with the follow-up protocol (language difficulties, severe psychiatric disorder, cognitive impairment, drug addiction)Intra-articular corticosteroids in the affected joint within 3 months prior to enrolment

### Who will take informed consent? {26a}

Consulting surgeons at the respective department will obtain written informed consent from all participants. The study’s purpose, methods, potential benefits, and risks will be explained. Participants can decline or withdraw their consent at any time during the study.

### Additional consent provisions for collection and use of participant data and biological specimens {26b}

N/A. This study will not involve the collection of biological specimens.

## Interventions

### Explanation for the choice of comparators {6b}

This trial will compare two different treatment concepts for patients with wrist OA: (1) Surgical treatment with partial wrist denervation of AIN and PIN and to (2) nonsurgical treatment including patient education and a self-managed exercise therapy program. We have chosen patient education and exercise therapy as a comparator, as this is considered core treatment for all individuals with OA.

### Intervention description {11a}

#### Partial wrist denervation

Surgery is conducted under local anaesthesia and bloodless field or wide-awake local anaesthesia no tourniquet (WALANT) according to the surgeon’s preference. AIN and PIN neurectomy is performed through a single dorsal incision as described by Berger [5]. Anatomical studies of the branches of the AIN have raised concerns about potential denervation of all motor branches to the pronator quadratus muscle (PQ) when the denervation technique by Berger is used [26]. To ensure that the PQ is not completely denervated, the AIN is traced distally within 2 cm of the ulnar head, and only 1 cm of the AIN is resected at this level to protect the motor function of the PQ. The skin is closed by resorbable or non-resorbable sutures according to surgeons’ preferences. Active motion of the operated joint starts immediately after surgery as tolerated by the participant. No formal hand therapy protocol is used, and participants do not receive any specific rehabilitation program (orthoses, education, exercise) after surgery, as this is standard care for this minor surgical procedure. Non-resorbable sutures are removed by a nurse at the clinic 2 weeks postoperatively, and the wound is screened for signs of infection.

#### Patient education and a self-managed exercise therapy program

The control intervention includes patient education and a revised self-managed exercise therapy program based on Larsson et al.’s protocol [23, 27]. The patient education contains information about wrist OA pathophysiology, the rationale behind exercise treatment, self-management strategies, pain management, and activity modification principles. In addition, participants are provided with a wrist orthosis along with usage instructions. The exercise therapy program aims to improve wrist stability, protect the joint, strengthen core muscles controlling the wrist, and engage the entire arm for more proximal muscle engagement [28–30]. It starts with isometric and grip-strength exercises and then introduces resistance training with a TheraBand for the elbow and shoulder while maintaining a stable wrist position, after 2 weeks. This differs from the protocol by Larsson et al., which focused solely on the affected wrist [27]. The exercise therapy program is performed at home, twice daily for 12 weeks, with follow-up assessments by the treating physiotherapist (PT) at 2, 6, and 12 weeks. A detailed description of the education and exercise therapy program can be found in Appendix 1.1.

### Criteria for discontinuing or modifying allocated interventions {11b}

To ensure that the participants can continue with the exercise therapy program without experiencing increased pain, the treating PT may need to make minor individualized adjustments to the exercise program, such as decreasing the number of repetitions or adjusting the load of the isometric exercises.

### Strategies to improve adherence to interventions {11c}

Compliance with the exercise program will be emphasized at all follow-ups, and participants will track their adherence using an exercise diary (Appendix 1.1).

### Relevant concomitant care permitted or prohibited during the trial {11d}

Intra-articular corticosteroids are allowed during follow-up but must not be administered within 3 months prior to a study assessment. Participants are allowed to continue with non-prescription analgesics as needed. The type, dosage, and frequency of analgesic use will be documented at each study assessment.

### Provisions for posttrial care {30}

Participants requiring posttrial treatment will be offered standard care for wrist OA at their respective hand surgery clinics. Those affected by treatment-related complications may seek compensation from the Swedish patient insurance system (LÖF).

### Outcomes {12}

#### Primary outcome measure

The primary outcome is the change of PRWE score [31] with a primary endpoint at 6 months following the start of the intervention. The PRWE is a wrist-specific PROM designed to assess pain and disability in daily activities over the past week. It consists of a pain subscale (5 items) and a function subscale (10 items), with a total score ranging from 0 to 100, where a higher score indicates greater disability. The PRWE is a valid and reliable tool for assessing wrist and hand injuries [32], with strong psychometric properties in wrist OA [33]. The validated Swedish version of the PRWE will be used [34].

#### Secondary outcome measures

##### Wrist range of motion (goniometer)

The range of wrist motion (flexion, extension, radial deviation, ulnar deviation, pronation, and supination) of the affected wrist will be measured with a goniometer according to standardized instructions [35].

##### Grip strength (Jamar dynamometer)

Grip strength in both hands will be assessed using a Jamar dynamometer as outlined in standardized instructions [35]. Each hand will be tested in three trials, and the mean grip strength, recorded in kilograms (kg), will be calculated for each hand.

##### The Numerical Pain Rating Scale (NPRS)

The NPRS is an 11-point Numerical Pain Rating Scale (0–10), where 0 represents no pain and 10 represents the worst pain imaginable [36]. Participants choose a value that best reflects the intensity of pain they have experienced in the affected wrist over the past week. This study will evaluate two pain measures: (1) pain at rest and (2) pain on load.

##### EQ-5D-5L (Health Quality-of-Life Measure)

The EQ-5D-5L is a standardized questionnaire created by the EuroQol Group to assess health-related quality of life (HRQoL) across five domains: mobility, self-care, usual activities, pain/discomfort, and anxiety/depression, where each question is rated on five levels [37]. A summary score from 0 to 1 is calculated based on population reference data from Sweden [38]. In addition to the five domains, the EQ-5D-5L includes the EQ Visual Analogue Scale (EQ VAS), which measures self-rated health on a 20-cm vertical scale. This scale is marked at each endpoint with the phrases “the best health you can imagine” and “the worst health you can imagine”.

##### Pain Catastrophizing Scale (PCS)

The PCS is a PROM that assesses catastrophic thinking related to pain and its potential effects on emotional and physical functioning [39]. The questionnaire comprises 13 items, each scored on a 5-point Likert scale, ranging from 0 (“Not at all”) to 4 (“All the time”). The total score can range from 0 to 52, with higher scores indicating increased levels of pain catastrophizing.

##### Global Rating of Change (GROC)

The GROC score consists of a single question asking participants to rate how their condition has changed since the start of treatment [40]. The responses are recorded on an 11-point self-report Likert scale, ranging from −5 to +5, where “−5” indicates “a very great deal worse”, “0” represents “about the same”, and “+5” signifies “a very great deal better”. In this study, the question is phrased: “Considering the problems with your wrist, how would you describe your wrist now compared to before the training period or denervation surgery?”.

#### Complications

The presence of complications to the surgical treatment, such as wound infections or wound dehiscence, will be assessed at the wound check 2 weeks postoperatively and at the 3-month study assessment.

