## Assignment of interventions: blinding

### Who will be blinded {17a}

Independent hand surgeons, responsible for the follow-up measurements at 3, 6, and 12 months after intervention, will remain blinded to treatment allocation. Participants in both groups will wear a Tubigrip, glove, or bandage on the wrist during all assessment visits, preventing the assessor from determining whether the participant has undergone surgery. The blinded assessor is not allowed to access the medical journal until the measurements are completed and recorded in the study protocol. After the assessment, the evaluating hand surgeon may access the medical journal, remove the Tubigrip, and discuss further treatment options with the participant, if necessary. Additionally, data analysts will also be blinded to treatment allocation.

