### Plans to promote participant retention and complete follow-up {18b}

All post-enrolment appointments are provided free of charge. Participants are scheduled for regular follow-up visits to support retention. Participants who miss scheduled appointments will be contacted by phone and/or mail to reschedule. Those who are unable or unwilling to attend in-person follow-up assessments are offered the option of a video consultation. Participants who decline both in-person and video assessments are asked to complete the PROMs and return them by mail. In the event of a dropout, reasons for discontinuation will be recorded, and all data collected up to that point will be retained and analysed. Participants who withdraw after inclusion but before undergoing the intervention will be replaced. In the exercise therapy group, regular follow-ups with the treating PT will support adhering to the program and enhance retention.

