### Adverse event reporting and harms {22}

All adverse events that may be associated with the interventions will be registered. If an adverse event occurs outside of scheduled follow-ups, participants are encouraged to contact their Department of Hand Surgery. If interim analyses reveal a high frequency of unexpected complications, early termination of the study may be considered. Study participants are covered by LÖF.

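### Complication checks are scheduled only for surgery and only up to month 3, so harms are ascertained unequally between the arms and mainly passively afterwards

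*Protocol article*

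**What the plan says.** All references are to the protocol article.

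- **Outcomes {12}, Complications.** The outcome is limited to the surgical treatment: "The presence of complications to the surgical treatment, such as wound infections or wound dehiscence, will be assessed". Its timing is "at the wound check 2 weeks postoperatively and at the 3-month study assessment". The examples are wound events.
- **Adverse event reporting and harms {22}.** The scope is both interventions, with no time limit: "All adverse events that may be associated with the interventions will be registered". For events between visits, participants are encouraged to contact their department. A high frequency of unexpected complications at an interim analysis may lead to early termination being considered.
- **Plans for assessment and collection of outcomes {18a}.** Complications are also retrieved from medical records, with no limit by arm or time.
- **Who will be blinded {17a}.** Blinded surgeons are "responsible for the follow-up measurements at 3, 6, and 12 months after intervention", in both arms.
- **Intervention description {11a}.** The exercise arm meets the physiotherapist at 2, 6 and 12 weeks. In the surgical arm, "Non-resorbable sutures are removed by a nurse at the clinic 2 weeks postoperatively", and the same sentence contains the wound screen. This section also gives protection of the pronator quadratus motor supply as the reason for limiting the nerve resection.
- **Criteria for discontinuing or modifying allocated interventions {11b}.** Program adjustments by the physiotherapist are allowed: "To ensure that the participants can continue with the exercise therapy program without experiencing increased pain".
- **Plans to promote participant retention {18b}.** Those who decline both in-person and video assessment "are asked to complete the PROMs and return them by mail".

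**The concern.** Two arms can be described side by side for harms only if both are asked the same questions at the same times. Here one arm has a scheduled complications outcome and the other has none, and the scheduled outcome ends a quarter of the way through follow-up. Events found by looking would be set beside events found because someone reported them.

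Three features of the protocol make this matter. Its closing discussion counts few complications among the advantages that would make denervation attractive if it proves superior, and elsewhere describes exercise as free of reported adverse effects; unequal collection cannot test either statement fairly. The interim safeguard in the adverse event section is only as good as the harms data that reach it. And the protocol itself names a motor risk of the operation, while the complications it gives as examples are all wound events.

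The distortion could run either way: early wound events are sought only after surgery, whereas later, sensory or motor events depend on being volunteered or written in a record.

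**Working it through.** The plan states no figure on this point, so the check is a comparison of sections, followed by a note on precision.

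**1. Follow-up contacts and stated complication checks.**

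| | Surgical arm | Exercise arm |
|---|---|---|
| Stated follow-up contacts | 2 weeks; 3, 6, 12 months (4) | physiotherapist at 2, 6, 12 weeks; 3, 6, 12 months (6) |
| Contacts with a stated complication check | 2 weeks, 3 months (2) | none (0) |
| Follow-up after the last stated check | 12 − 3 = 9 months; 9/12 = 75% | not applicable |

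The zero counts stated complication checks, not contacts. The exercise arm is seen at least as often as the surgical arm.

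**2. Do the wider sections close the gap?** Adverse event reporting {22} covers both interventions, but the means it states is that the participant makes contact. Data collection {18a} adds medical records, which hold only what was asked about or reported. Both widen the scope. Neither adds a scheduled enquiry in the exercise arm, or in either arm at 6 or 12 months.

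**3. What the common outcome measures show.** PRWE, pain ratings at rest and on load, and the global rating of change are collected alike in both arms at 3, 6 and 12 months. They capture worsening symmetrically, but they do not identify an adverse event or its type. Pronation range by goniometer and grip strength give an indirect view of motor loss; neither isolates pronator quadratus strength.

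**4. Mail responders.** They return PROMs only, and none of the PROMs described asks about complications.

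**5. The 2-week wound check.** The intervention section mentions wound screening together with removal of non-resorbable sutures, and either suture type is allowed. The Complications section refers to a 2-week wound check without a suture condition. The two passages can be read differently and need reconciling.

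**6. Precision, for context only.** The planned size is 70 per arm.
- If no event is observed in 70 participants, the one-sided 95% upper bound is 1 − 0.05^(1/70) = 0.042, or 4.2%.
- With assumed true rates (the documents give none), the power of a two-sided 5% comparison is Φ{[|p₁ − p₂| − 1.96·√(2p̄(1 − p̄)/n)] / √([p₁(1 − p₁) + p₂(1 − p₂)]/n)}, where p̄ is the mean of the two rates and n = 70.
- For 5% against 1%: (0.04 − 0.0565)/0.0286 = −0.58, power about 28%.
- For 10% against 2%: (0.08 − 0.0787)/0.0396 = 0.03, power about 51%.

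A formal test of harms would therefore be weak even with equal ascertainment. With counts this small, a few unrecorded events can also change the description.

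**The case against.** The strongest reply is that the adverse event section registers possibly related events for both interventions without a time limit, that records are searched in both arms, and that both arms are seen at 3, 6 and 12 months. Asking participants to call about events outside scheduled visits suggests that events coming up at visits are recorded there. The complication examples are introduced as examples, so a motor or sensory event is not excluded. The physiotherapist sees the exercise arm three times and must respond to increased pain. No between-arm comparison of harms is among the objectives. Finally, this is a condensed article: the SPIRIT figure is not shown, and the full protocol and case report forms, which may hold visit-level harms questions, are not at hand.

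Much of this stands, and it rules out stronger readings. A reader might infer that harms cannot be compared at all, that the exercise arm is never asked about harm, or that late and motor complications will be missed. The documents do not support these: silence about a question is not proof that it is never put, and general registration and records can still catch such events. A reader might also want to put a number on the lost events, but any capture rate would be invented.

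What the reply does not remove is what the text itself fixes: an outcome limited to one treatment, with two dated checks, beside a promise covering both treatments with no equivalent schedule.

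**Conclusion.** The concern holds as one of unequal and mainly passive ascertainment. The stated complications schedule covers one arm, 2 checks against 0, and leaves 9 of 12 months without one. Participants are not blinded, so willingness to report may differ between arms, and a description of harms by arm is open to ascertainment bias in either direction. Later, motor or sensory events may be under-recorded; the documents do not show that they will be.

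The primary endpoint and its analysis are unaffected. What is weakened is the safety statement that will accompany the result, and the complication data on which early termination might be considered. No size in events can be given.

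This conclusion assumes that the article's text describes the schedule as it is run. If the unseen figure, forms or full protocol already contain the same harms enquiry in both arms at every assessment, what remains is to correct the article's wording.

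**What to change.** **Change the Complications section.** Replace the surgery-only schedule after the early wound check with one participant-completed harms form, identical in both arms, at the existing 3-, 6- and 12-month assessments. It should hold an open question and fixed items on wound problems, altered sensation, weakness, flare of wrist pain, and new arm or shoulder symptoms. Include it in the PROM package so that mail responders complete it, and keep it from the blinded assessor until the measurements are recorded. Report harms by arm, in the same categories, over 12 months, descriptively and with confidence intervals.

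**Align the sections.** Use one adverse event definition in Complications, in data collection {18a} and in adverse event reporting {22}. Reconcile the intervention section with Complications on who receives the 2-week wound check; which reading applies is for the investigators to state.

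**Do not count physiotherapist program adjustments as events in themselves.** They may be preventive and have no surgical counterpart, so counting them would create a new asymmetry. A pain flare reported on the common form is counted in either arm.

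**Cost.** A short extra form and an ethics amendment, with no new visits. Reported event counts will probably rise. Recruitment began in March 2024 and is estimated to end in 2027, so participants already past some visits will have mixed ascertainment. The report should state how many, by arm, and from which visit the form was used.
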